**Figure 2 figure2:**
[figure not shown]
Randomized controlled trial study flow (phase 3).

All participant data collection will occur electronically. Informed consent will be collected via Adobe Sign (Adobe Inc), and self-report data will be collected through a standardized Qualtrics (Qualtrics International Inc) survey. Pre- and postintervention data collection, which will occur in clinics, will be conducted with iPads (Apple Inc) that are dedicated to the study site. Data will be immediately uploaded to a secure database through wireless connectivity. Self-report data to be collected at 2 and 6 months post intervention will be captured by using the same standardized Qualtrics survey that will be used in clinics; the direct survey link will be shared via text or email, depending on the participants’ preferences.

We will conduct exit interviews with clinic health providers to assess barriers and facilitators to implementation specifically to inform regional dissemination.

### Effectiveness Data

Data on clinic-level vaccination rates and vaccination series completion rates will be collected prior to the start of the study and once per year thereafter. Patient-specific data will be collected at the end of the 6-month study cycle.

### Medical Records

We propose to collect data on vaccination from medical records at partner clinics. We will request records from partner clinics, and a member of each clinic will extract them for evaluation. The research team will review medical records for evidence that participants accepted vaccination during the 6-month study period, as well as evidence of whether the participants completed the vaccine series.

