### Recruitment

For the first and second phases of the study, participants will be recruited through our health care partner—the University of Alabama at Birmingham Selma Family Medicine clinic—and their local community–based network, which includes high schools and nonprofit agencies. During the third phase, in which the newly crafted intervention will be tested, participants will be recruited in enrolled clinics. Screening for eligibility (eg, vaccine status, age, etc) will occur via self-report and be corroborated via clinical record and immunization registry verification.

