### Phase 3: Intervention Evaluation

We will conduct a pilot hybrid type 1 effectiveness-implementation cluster-randomized controlled trial [20] to assess intervention acceptability and feasibility (clinics: N=4; adolescents: N=120). The cluster-randomized controlled trial design minimizes the risk of contamination among participants in different arms and is ideal when settings are similar in terms of population characteristics. These trials are frequently used when interventions are to be carried out at the level of whole groups. Implementation science hybrid designs assess intervention effectiveness in real-world settings and document barriers and facilitators to delivery and sustainability [20]. Considering that our goal is to disseminate the intervention widely, we must understand the contexts that influence success and failure, so that we can plan for them and mitigate weaknesses accordingly.

We will enroll 120 adolescents across 4 clinics; 2 clinics will be randomized to implement the intervention condition, and 2 clinics will be randomized to a time-attention control. All African American patients unvaccinated for HPV (aged 15-26; all genders) will be approached to enroll in the study when they come in for a visit, regardless of the purpose of that clinical visit. After informed consent is collected from adolescents, we will collect preintervention, immediately postintervention, 2-month postintervention, and 6-month postintervention survey data related to the behavior change objectives -- increased knowledge of vaccines, reduced stigma, and increased motivation, which all result in improved vaccine confidence and higher vaccination rates — in addition to participant demographics and known potential associates of vaccination or vaccine hesitancy. We will collect design metrics to assess feasibility and acceptability, informed by the Bowen framework [27] (Figure 2).

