### Phase 3: Data Management and Quantitative Analysis

A descriptive analysis of all study feasibility and outcome variables will be summarized by using means and SDs for continuous measures and frequencies and percentages for categorical measures. Between-group differences will be compared by using standard 2-tailed cluster analyses. Further, 2-sample tests for proportions [28] will be used to compare initial vaccination acceptance, the indication of dose completion, and study dropout. An adjusted McNemar test [29] will be used to determine if the intervention group had any changes in vaccine knowledge post intervention. Similar analyses will be used in the control group, and the two groups’ changes will be examined. For any continuous measure (eg, stigma), 2-sample *t* tests [30] will be used, and appropriate assumptions will be validated. Factors related to unexpected design or study implementation issues, such as systematic enrollment issues at clinics or differential times between patients’ first visit and their follow-up resulting from issues beyond common follow-up issues, will be assessed. If it is determined that these issues require analysis adjustment, we will use generalized estimating equations to compare group differences in all measures while adjusting for these factors. Generalized estimating equations require all missing data to be missing completely at random; however, as our primary outcome relates to initial vaccination acceptance, we do not expect any missingness. Likewise, we will assume that study dropout is an indicator of incomplete dosing. Missing values for other outcomes will be examined, and if missingness at random can be assumed, multiple imputations [31] will be used.

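### Partner-clinic records are the only source named for the vaccination outcome, so doses given elsewhere may be missed; the registry check used at screening is not extended to it

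*Protocol article*

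**What the plan says.** Under Medical Records, the Protocol article gives the source of the vaccination outcome: "We propose to collect data on vaccination from medical records at partner clinics". On extraction: "We will request records from partner clinics, and a member of each clinic will extract them for evaluation". On what is judged from them: "The research team will review medical records for evidence that participants accepted vaccination during the 6-month study period", followed by whether the series was completed. The section mentions no registry and no other provider.

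Under Recruitment, screening for eligibility, including vaccine status, will "occur via self-report and be corroborated via clinical record and immunization registry verification". The registry is mentioned nowhere else in the article.

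Under Phase 3: Data Management and Quantitative Analysis, two assumptions govern incomplete information on this outcome. For acceptance: "as our primary outcome relates to initial vaccination acceptance, we do not expect any missingness". For completion: "we will assume that study dropout is an indicator of incomplete dosing".

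Under Phase 3: Intervention Evaluation, surveys are planned before, immediately after, and 2 and 6 months after the intervention, on objectives described as "increased knowledge of vaccines, reduced stigma, and increased motivation, which all result in improved vaccine confidence and higher vaccination rates". The article does not say that these surveys ask about doses received or contribute to the vaccination outcome.

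**The concern.** Vaccine status is established from a wider set of sources at entry than at outcome. A youth vaccinated outside the partner clinic during follow-up may leave no entry in the chart that is reviewed. Because no missing data are expected, the plan has no category for a dose that was given but not seen, and such a youth would by default be analysed as not having accepted. The dropout assumption does the same for completion: someone who leaves the study and finishes the series elsewhere is taken to be incomplete.

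The design leaves room for such doses. Youths are approached at a visit made for any reason, so the partner clinic need not be where they receive vaccines. The intervention continues after the visit through text reminders. The trial also aims at COVID-19 vaccine acceptance. At stake is the outcome that the article calls primary, together with the early indication of effectiveness and the effect size that the pilot is meant to supply.

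**Working it through.** **1. The sources side by side**

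| Purpose | Sources named | Section |
|---|---|---|
| Vaccine status at screening | Self-report, clinical record, immunization registry | Recruitment |
| Acceptance over 6 months and series completion | Partner-clinic medical records | Medical Records |
| Participant with no recorded dose | No category; no missing data expected on initial acceptance | Phase 3: Data Management and Quantitative Analysis |
| Dropout | Taken as incomplete dosing | Phase 3: Data Management and Quantitative Analysis |

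That a participant without a recorded dose is analysed as not accepting is an inference from the second and third rows. The article does not state it as a rule.

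**2. Which part of the outcome is exposed**

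A dose accepted at the enrolment visit is given in the partner clinic and should be in its record. A first dose later in the 6 months, or a further dose in the series, could be given anywhere. The analysis section speaks of initial acceptance, while Medical Records assesses acceptance over the whole 6 months, so how much of the primary outcome is exposed depends on which reading applies. Series completion is exposed on either.

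**3. Illustrative size**

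The article states no expected acceptance rate and no share of doses given elsewhere, so there is no figure to reproduce. All rates below are assumptions.

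Formula: recorded proportion = true proportion × (1 − share missed). This supposes that no dose is recorded falsely.

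*Equal under-capture, true rates 20% (control) and 40% (intervention):*

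| Share missed | Control | Intervention | Difference |
|---|---|---|---|
| 0% | 20% | 40% | 20 points |
| 10% | 0.20 × 0.9 = 18% | 0.40 × 0.9 = 36% | 18 points |
| 30% | 0.20 × 0.7 = 14% | 0.40 × 0.7 = 28% | 14 points |
| 50% | 0.20 × 0.5 = 10% | 0.40 × 0.5 = 20% | 10 points |

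The difference shrinks in proportion to capture. The ratio of the two rates stays at 2 throughout.

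*Unequal under-capture, no true effect (20% in both arms):*

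- Missed 40% in control and 20% in intervention: 0.20 × 0.6 = 12% versus 0.20 × 0.8 = 16%, a spurious 4 points in favour of the intervention.
- Missed 20% in control and 40% in intervention: 16% versus 12%, a spurious 4 points against it.

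With 30% in both arms, capture of 70% in one arm and 90% in the other gives 21% versus 27%, a spurious 6 points towards the better-captured arm.

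**The case against.** The strongest reply is that a condensed article need not list every outcome source or say how outside doses are coded. The Medical Records section excludes no other source, the 2- and 6-month surveys might ask about vaccination, and clinic charts may hold doses reported from elsewhere. This stands to the extent that exclusive reliance on clinic charts cannot be asserted; what can be said is that they are the only source named. It does not dispose of the point, because the article positively states an outcome source and a no-missingness expectation, and names a fuller source only for screening.

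A second reply is that the article ties its no-missingness statement to initial acceptance. If that means acceptance at the enrolment visit, the clinic record will show it. This also stands, and it moves the weight of the point to later acceptance and series completion.

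A third is that the rates are invented and that the share given elsewhere may be small, since the Background describes these counties as having poor access to care. The size is indeed unknown, and the figures above show only how the mechanism works.

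Two stronger readings are tempting. A reader might infer that doses given elsewhere are counted as refusals. No such rule appears, and the only refusals the article mentions are refusals to take part in the study. A reader might also infer that the error favours the intervention, because an in-clinic programme brings vaccination forward to the index visit. The text reminders could equally prompt intervention youths to be vaccinated elsewhere, so the documents support neither direction.

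**Conclusion.** The point holds in a limited form. The article names partner-clinic records as its only source for the vaccination outcome, provides no category for unobserved doses, and does not carry the screening registry check through to the outcome. Doses given elsewhere may be missed and analysed as not accepted or not completed, mainly after the index visit and for series completion.

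Its size cannot be determined from the documents. If true rates were 20% and 40%, equal under-capture of 10% to 50% would leave 18 to 10 of the 20 points. If capture differed by arm, the bias could go either way. No sample-size figure in the article depends on this. It is worth correcting because the remedy is specific, cheap, and uses a source the trial already consults.

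**What to change.** Define initiation and completion, separately for each vaccine, as any dose dated within the follow-up window in the partner-clinic record or the immunization registry. Query the registry at 6 months in the same way for all 120 participants in both arms, including those who dropped out where their consent allows it, so that completion in dropouts is looked up where possible and not assumed. Use self-report at 2 and 6 months only to flag discrepancies for checking. State also whether initial acceptance refers to the index visit or to the whole 6 months.

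The cost is one further look-up per participant, about 120 in all, and possibly a line in the consent. The article does not say who performs the registry check at screening, so staff time should be confirmed. So should coverage of COVID-19 doses, because the stated eligibility criterion concerns HPV vaccination.

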### Feasibility Data (The Bowen Model [27])

Clinic staff will maintain logs on acceptances and refusals to study participation. We will use these data to assess if the study procedures and protocols are feasible and the intervention is acceptable (Table 1).

**Table 1 table1:** Components of the Bowen model [27].

Component	Assessment focus	Sample outcomes
Demand	Documenting the use of the intervention	Fit within organizational culture and perceived effects and demand
Acceptability	Health providers’ and patients’ reactions to the intervention	Satisfaction, intent to continue use, and perceived appropriateness
Implementation	Extent to which the intervention is implemented as planned	Degree of execution and resources for implementation
Practicality	Extent to which intervention can be implemented in rural Alabama	Cost analysis factors affecting implementation
Adaptation	Modifications needed to accommodate the context	Degree to which outcomes are obtained with the mobile format
Integration	Level of system change for integrating the intervention	Perceived fit with infrastructure and perceived sustainability
Expansion	Potential success of the intervention in a different setting	Fit with the local goals and culture
Limited efficacy testing	Small-scale implementation	Effect size estimation and effects on key intermediate variables

### Implementation Data

At 4 months after the start of the trial, we will solicit feedback from staff who were interviewed in the initial qualitative phase (estimated number of staff members: range 4-8). We will collect data on the inner and outer contexts affecting implementation and data on the policies, environments, funding, and social conditions that influenced intervention delivery; this interview will take about 1 hour. We will also conduct in-depth exit interviews with a purposively selected group of adolescent participants on a rolling basis after they have concluded the 6-month study cycle (number of participants: range 6-12). The interviews will collect data on how the intervention was experienced and internalized. We will ask questions on how sociocultural nonintervention contexts affected the likelihood of vaccination and series completion. These data will provide a direct look into real-world implementation considerations affecting African American adolescents.

### Phase 3: Data Management and Quantitative Analysis

A descriptive analysis of all study feasibility and outcome variables will be summarized by using means and SDs for continuous measures and frequencies and percentages for categorical measures. Between-group differences will be compared by using standard 2-tailed cluster analyses. Further, 2-sample tests for proportions [28] will be used to compare initial vaccination acceptance, the indication of dose completion, and study dropout. An adjusted McNemar test [29] will be used to determine if the intervention group had any changes in vaccine knowledge post intervention. Similar analyses will be used in the control group, and the two groups’ changes will be examined. For any continuous measure (eg, stigma), 2-sample *t* tests [30] will be used, and appropriate assumptions will be validated. Factors related to unexpected design or study implementation issues, such as systematic enrollment issues at clinics or differential times between patients’ first visit and their follow-up resulting from issues beyond common follow-up issues, will be assessed. If it is determined that these issues require analysis adjustment, we will use generalized estimating equations to compare group differences in all measures while adjusting for these factors. Generalized estimating equations require all missing data to be missing completely at random; however, as our primary outcome relates to initial vaccination acceptance, we do not expect any missingness. Likewise, we will assume that study dropout is an indicator of incomplete dosing. Missing values for other outcomes will be examined, and if missingness at random can be assumed, multiple imputations [31] will be used.

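### The analysis text promises cluster analyses but names two-sample tests without saying that they account for clinic, and commits to no method that holds its level with 4 randomised clinics

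*Protocol article*

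**What the plan says.** The protocol article, under Phase 3: Intervention Evaluation, makes the clinic the unit of randomisation: "2 clinics will be randomized to implement the intervention condition, and 2 clinics will be randomized to a time-attention control". The sample is given as a plain count: "We will enroll 120 adolescents across 4 clinics".

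Under Phase 3: Data Management and Quantitative Analysis, four statements bear on the comparison of arms:

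- A general one: "Between-group differences will be compared by using standard 2-tailed cluster analyses". No cluster method is named.
- Directly after it, the test for the binary outcomes: "Further, 2-sample tests for proportions [28] will be used to compare initial vaccination acceptance, the indication of dose completion, and study dropout". Initial acceptance is the primary outcome: "our primary outcome relates to initial vaccination acceptance, we do not expect any missingness".
- For scales: "For any continuous measure (eg, stigma), 2-sample *t* tests [30] will be used, and appropriate assumptions will be validated".
- GEE is to be used if unexpected design or implementation problems call for adjustment, and it then adjusts for those factors. It is not presented as the routine way to handle clinic.

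A McNemar test for change in knowledge is described as adjusted, but the text does not say for what. The article gives no ICC, alpha, power or degrees of freedom.

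**The concern.** Youths from one clinic share staff, community and local vaccine supply, so their outcomes are likely to be correlated. With 2 clinics per arm, the difference between arms also contains the difference between clinics, and only 4 − 2 = 2 degrees of freedom are available to measure it.

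A test that ignores this, or that estimates the clinic variation and then uses a normal or chi-square reference, can mistake clinic differences for an intervention effect. The general sentence points to a cluster analysis. The sentences that name the tests do not say so, and they are the ones an analyst would follow.

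What is at stake is the effectiveness signal that the abstract promises and the effect size estimate listed in Table 1. Both feed any decision to scale up.

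**Working it through.** The article states no power or precision figure, so there is none to reproduce. The check asks what error rate each admissible reading of the text would give.

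**Inputs from the article:** 4 clinics, 2 per arm; 120 youths; two-sided tests; binary primary outcome.

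**Assumptions:** nominal level 5%; equal clinics of m = 120/4 = 30, so 60 per arm; 20% acceptance in both arms (the article's state-wide series-completion rate, used only as an illustration); ICC 0.01, 0.05 and 0.10.

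**1. Youths treated as independent.** The design effect is DE = 1 + (m − 1) × ICC = 1 + 29 × ICC, which gives 1.29, 2.45 and 3.90. Type I error is 2 × [1 − Φ(1.96/√DE)]:
- ICC 0.01: 1.96/√1.29 = 1.73, error 0.084
- ICC 0.05: 1.96/√2.45 = 1.25, error 0.211
- ICC 0.10: 1.96/√3.90 = 0.99, error 0.321

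A beta-binomial simulation with 200,000 runs gave 0.084, 0.213 and 0.330.

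**2. ICC-adjusted test with a large-sample reference.** Simulation with negative ICC estimates set to 0 gave 0.057, 0.111 and 0.139. Without that truncation it gave 0.18 to 0.19 at every ICC. The second result can be checked by hand. The statistic then behaves like t on 2 df, for which P(|T| > t) = 1 − t/√(t² + 2). At t = 1.96 this is 1 − 1.96/√5.84 = 0.19.

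**3. GEE fallback, independence working correlation, uncorrected sandwich variance.** With 2 equal clinics per arm, the sandwich divides each arm's sum of squared clinic deviations by 4, where the unbiased variance of the arm mean divides by 2. The standard error is too small by a factor of √2, so the test rejects when |T| > 1.96/√2 = 1.386. The error is 1 − 1.386/√(1.921 + 2) = 0.30. The ICC does not enter. Simulation also gave about 0.30 at every ICC, including 0.

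**4. t test on the 4 clinic proportions, 2 df.** The critical value is 4.303. Simulated error was 0.048, 0.050 and 0.053.

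| Analysis | ICC 0.01 | ICC 0.05 | ICC 0.10 |
|---|---|---|---|
| Youths as independent | 8% | 21% | 33% |
| ICC-adjusted, large-sample (negative ICC set to 0) | 6% | 11% | 14% |
| GEE, uncorrected sandwich | 30% | 30% | 30% |
| Clinic-level t, 2 df | 5% | 5% | 5% |

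**5. A rough ICC from the article's own figures.** The Background says that many Alabama counties lie between 10% and 25%. Taken as uniform, the variance is 0.15²/12 = 0.001875 around a mean of 0.175. The ICC is then 0.001875/(0.175 × 0.825) = 0.013, DE = 1.377, and the error of the unadjusted test is about 9.5%. This uses county series completion as a stand-in for clinic-level first acceptance, so it is weak evidence.

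**6. Interval width for 20% v 40%.** If youths are independent, the half-width is 1.96 × √[(0.16 + 0.24)/60] = 0.16. On 2 df it is 4.303 × √[(0.16 + 0.24) × DE/60] = 0.40, 0.55 and 0.69.

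**7. What a test could show.** Power for 20% v 40% is nominally 0.67 if youths are independent, and about 0.24, 0.16 and 0.12 on 2 df. A randomisation test over the C(4,2) = 6 allocations cannot give a two-sided p below 2/6 = 0.33.

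**The case against.** A reader might infer that the plan is to analyse the 120 youths as independent, so that its p-values will be far too optimistic. The article does not say that:

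- It announces "standard 2-tailed cluster analyses" immediately before the named tests, and those tests may be meant as the detail of that sentence.
- A two-sample t test on clinic means is still a two-sample t test.
- The sources cited for the tests are not at hand. Whether they describe cluster-adjusted versions, and with what reference distribution, cannot be settled.
- The inflation is modest at the only ICC that can be drawn from the article: about 9.5% unadjusted, and 6.4% for the truncated adjusted test. The 21% and 33% figures need ICC values that the article does not contain.
- The article labels a primary outcome but no secondary ones, and this section states no alpha, interval or decision rule. A prediction that significance would often be claimed goes beyond the text.
- This is a pilot for acceptability and feasibility, and an article may leave degrees of freedom to the full plan.

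Most of this stands, and it makes the point conditional. It does not remove it. The article does fix the names of the tests, and for the primary outcome and the scales it does so without mentioning clinic. The one correlated-data model it names is conditional and, if uncorrected, misses its level at every ICC. The pilot aim lowers the weight on p-values, but tests and an effect size are planned, and the abstract's conclusions speak of the intervention being found efficacious.

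**Conclusion.** The concern holds as an ambiguity with consequences. The analysis section does not make clear that the comparisons of acceptance, dose completion, dropout and the continuous measures account for clinic, and it does not commit to a method that holds its level with 2 clinics per arm.

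The size is conditional on the reading and on the ICC. An unadjusted analysis is mildly liberal at ICC 0.01 and badly so at 0.05 to 0.10. A large-sample adjusted test is close to nominal at 0.01 but not at 0.05 or above. The uncorrected GEE fallback is at about 30% throughout. These figures rest on equal clinics of 30, 20% acceptance and a two-sided 5% level, all of them assumptions apart from the two-sided testing. Of the analyses checked, only the clinic-level one on 2 df held close to 5% across the range.

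**What to change.** State in Phase 3: Data Management and Quantitative Analysis that every between-arm comparison is made at clinic level. The clinic proportion or mean is the observation, and the difference is given with a 95% CI from the t distribution on 2 df. A mixed model with 2 between-clinic degrees of freedom is an equivalent choice. Say that the named two-sample tests are meant in this sense, or remove them. Do not rely on GEE with an uncorrected sandwich variance as the fallback. Report the vaccination signal as an estimate with this interval and make no significance claims.

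The change is to wording only and needs no new data or design. The cost is precision. For 20% v 40%, the half-width becomes about 40 to 69 points at ICC 0.01 to 0.10, in place of the 16 points obtained if youths are treated as independent. That width reflects what 4 clinics can show about effectiveness.

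### The primary comparison of initial vaccination acceptance uses no baseline covariate although suitable ones are collected, so chance differences in participant mix between four clinics add avoidable noise to the effect estimate

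*Protocol article*

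**What the plan says.** All statements are in the protocol article; no separate analysis plan is at hand.

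- **Primary outcome.** Phase 3: Data Management and Quantitative Analysis identifies it in passing: "as our primary outcome relates to initial vaccination acceptance, we do not expect any missingness".
- **Test.** The same section says that "2-sample tests for proportions [28] will be used to compare initial vaccination acceptance, the indication of dose completion, and study dropout". The sentence before it is general: "Between-group differences will be compared by using standard 2-tailed cluster analyses". Neither names a participant covariate.
- **When adjustment is allowed.** The trigger is "Factors related to unexpected design or study implementation issues, such as systematic enrollment issues at clinics or differential times between patients’ first visit" and follow-up. Then: "If it is determined that these issues require analysis adjustment, we will use generalized estimating equations to compare group differences in all measures", adjusting for those factors.
- **What is collected.** Phase 3: Intervention Evaluation says "we will collect preintervention, immediately postintervention, 2-month postintervention, and 6-month postintervention survey data related to the behavior change objectives". The objectives are "increased knowledge of vaccines, reduced stigma, and increased motivation", and these data come "in addition to participant demographics and known potential associates of vaccination or vaccine hesitancy".
- **Design.** The same section plans 120 participants in 4 clinics, 2 clinics per arm. Ages run from 15 to 26, all genders are eligible, and the purpose of the visit does not matter. No matching or stratification of clinics is stated.

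**The concern.** The trial collects, before the intervention, variables that it regards itself as related to vaccination. It then assigns its primary outcome a test that has no place for them. Everyone is HPV-unvaccinated at entry, so the outcome has no baseline value of its own. Surveyed motivation, age and gender are among the nearest available predictors.

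Four clinics split two and two give only six possible allocations, so randomisation cannot be relied on to even out participant mix in the one allocation that is drawn. Any difference in mix then enters the observed arm difference.

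At stake is the clinical signal of effectiveness named in the Abstract and the effect-size estimation listed in Table 1 under limited efficacy testing. A noisy estimate could make the intervention look promising or unpromising because of who attended which clinic.

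**Working it through.** **No figure to reproduce.** The article states no sample-size calculation, significance level, acceptance rates, ICC or covariate effects. From the document come 4 clinics, 2 per arm and N = 120. Everything else below is assumed, including equal clinics of 30 (60 per arm).

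**Step 1: number of allocations.** 4!/(2! × 2!) = 6.

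**Step 2: how mix reaches the estimate.** For a binary baseline factor, the shift in the unadjusted difference is the arm imbalance in that factor times its effect on acceptance.
- Imbalance 10 points, effect 20 points: 0.10 × 0.20 = 2 points.
- Imbalance 20 points, effect 30 points: 0.20 × 0.30 = 6 points.
- Imbalance 30 points, effect 40 points: 0.30 × 0.40 = 12 points.

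With mean prevalence 50% and a between-clinic SD of prevalence of 10 to 20 points, the simulated mean absolute arm imbalance is about 11 to 17 points. It is about 7 points when clinics do not differ. The direction is random, so the shifts cancel over repeated randomisation but not in a single trial.

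**Step 3: spread of the estimate with no true effect (simulation).** Model: logit P(acceptance) = −1.2 + βx + clinic effect. The baseline score x has SD 1 and between-clinic ICC from 0.02 to 0.10, β runs from 0.7 to 1.3 per SD, and the clinic effect has SD 0 or 0.3. The raw arm difference is compared with the arm difference in clinic-level observed-minus-expected proportions. Ranges are over the settings.

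| | Unadjusted | Adjusted |
|---|---|---|
| SD of arm difference (percentage points) | 8-11 | 7-9 |
| Chance of a gap above 15 points | 6-18% | 4-11% |
| Mean raw difference | 0, within 1 point | – |
| Type I error, clinic-level t test | about 4-5% | about 4-6% |

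The raw difference moves in steps of 1/60, and 9/60 is exactly 15 points. The unadjusted tail probability therefore shifts by a few points according to whether such ties count. In the mildest setting the gain is slight (6.3% to 5.8% in one run).

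**Step 4: power of a clinic-level t test (2 df, two-sided 5%).** Assume 20% versus 40% acceptance.
- Mean outcome variance: (0.2 × 0.8 + 0.4 × 0.6)/2 = 0.20.
- Variance of a clinic mean: 0.20 × (1 + 29 × ICC)/30.
- With two clinics per arm, the variance of the arm difference is 2 × (that variance)/2, so its SE is the square root of the clinic-mean variance.
- Adjustment multiplies the variance by (1 − ρ²), where ρ is the covariate-outcome correlation.

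Example at ICC 0.01: 0.20 × 1.29/30 = 0.0086, SE 0.0927, noncentrality 0.20/0.0927 = 2.16, power 24%. With ρ = 0.5: 0.0086 × 0.75 = 0.00645, SE 0.0803, noncentrality 2.49, power 30%.

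| ICC | Unadjusted | ρ = 0.3 | ρ = 0.5 |
|---|---|---|---|
| 0.01 | 24% | 26% | 30% |
| 0.05 | 16% | 17% | 19% |
| 0.10 | 11.9% | 12.5% | 14.0% |

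This formula is generous, because it shrinks between-clinic variance too. If the covariate explains only within-clinic variation, the gain is about 0.4-1.1 points at ICC 0.05 and 0.1-0.4 points at ICC 0.10. Overall the gain is about 0 to 6 points.

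**The case against.** **It belongs in an analysis plan.** The choice of covariates is often left there, and the article never calls the comparison unadjusted. This has some force. But the article is not silent: it names the test for this outcome and gives its own rule for when adjustment happens, and that rule does not reach participants' baseline profile. The objection is to a stated choice.

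**The unadjusted comparison is legitimate.** This stands. A reader might infer that clinic mix biases the primary result or invalidates the test. The documents do not support that. Averaged over the randomisation the raw difference is centred on zero when there is no effect, and a clinic-level t test without covariates keeps its error rate.

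**Two larger figures are tempting but should not be used.**
- A participant-level z test that ignores clustering, with one measured factor as the sole source of clinic differences, gave type I error up to 16% unadjusted against about 5% adjusted. That is a clustering problem, which adjustment repairs there only because of how the scenario was built.
- For a participant-level test at 20% versus 40%, power rises from 69% to 73% (ρ = 0.3) and 81% (ρ = 0.5). This 4-12 point gain also ignores clustering, which the article's sentence on cluster analyses appears to address. The reference cited for the proportions test cannot be seen, so whether that test allows for clusters is unknown.

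**It is a pilot.** The main aims are acceptability and feasibility, so a simple comparison is defensible. That limits the severity. It does not remove the value of a steadier estimate from data already in hand.

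**Conclusion.** The point holds as an improvement in precision and in protection against chance imbalance, not as an error of validity. The plan fixes a covariate-free comparison for its primary outcome and reserves adjustment for other problems, while collecting variables that could sharpen the estimate.

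The benefit lies mainly in the effect estimate: an SD of about 7-9 rather than 8-11 percentage points, and a chance of a spurious gap above 15 points of about 4-11% rather than 6-18%. Power at clinic level barely moves.

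These sizes rest wholly on assumed acceptance rates, ICCs and covariate effects. With a weak predictor and similar clinics the gain is close to nil. The change is worth making because it is cheap, but nothing in the trial fails without it.

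**What to change.** In Phase 3: Data Management and Quantitative Analysis, make the primary estimate of the arm difference in initial vaccination acceptance adjusted for a few prespecified preintervention variables already collected, for example age, gender and the surveyed motivation measure. The article names no instrument for motivation, so the exact measure has to be specified.

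Use two stages:
1. Fit a logistic regression of acceptance on these covariates, without arm.
2. Compute observed-minus-expected acceptance for each clinic and compare these four values between arms.

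This spends no clinic-level degrees of freedom on covariates and avoids relying on generalized estimating equations with four clusters. Report the unadjusted clinic-level difference as a sensitivity analysis. Other adjusted analyses could serve; what matters is that one is fixed in advance.

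**Cost:** analysis wording only, with no new data, participants or staff. The covariates must be fixed before outcomes are seen and kept few, because acceptances among 120 youths may be few. Adjustment does not remove unmeasured or clinic-level differences, and the report should say so.
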